### 3.4 Sample size calculation

For this study the main outcome parameter is net glucose uptake by BAT after administration of salbutamol, as measured by dynamic  $^{18}\text{F}$ -FDG PET-CT scan.

Our sample size calculation is based on the results recently published by Blondin et al.[1] and Orava et al. [25]. Blondin et al. showed net glucose uptake by BAT as measured by dynamic  $^{18}\text{F}$ -FDG PET/CT after administration of the maximal allowable dose mirabegron (200 mg) of  $22 \pm 14$  nmol/g/min. We expect the effect of salbutamol on glucose uptake by BAT to be at least as big as the effect of the maximal allowable dose mirabegron. Orava et al. [25] showed net glucose uptake by BAT in thermoneutral condition of  $9 \pm 4$  nmol/g/min. Therefore, we predict the net glucose uptake of salbutamol in combination with propranolol to be comparable to the net glucose uptake by BAT in thermoneutral condition. Thus, we consider a difference in net glucose uptake by BAT of  $+13$  nmol/g/min after salbutamol administration as clinically relevant, with a SD of 10,  $\alpha = 0.01$ ,  $\beta = 80\%$ . Based on these parameters we need 10 subjects (<http://biomath.info/power/prt.htm>; based on Snedecor & Cochran, Statistical methods 7th edition).

In case a subject is withdrawn from the study before finishing all measurements, the investigator will try finding a replacement to maintain the initial population size.

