#### 7.1.2 Other study parameters

- Resting energy expenditure, as measured by indirect calorimetry
- Serum markers for lipid metabolism (triglycerides (TG), total cholesterol (TC), high density lipoprotein cholesterol (HDL-C), low density lipoprotein cholesterol (LDL-C), free fatty acids)
- Lipid pathway analysis using lipidomic analysis in plasma samples
- Serum markers for glucose metabolism (glucose, insulin)
- Circulating plasma BAT markers (e.g. microRNAs)

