### 7.3.2 Study days

This study encompasses two study days, both will take place in the LUMC. Subjects will be randomized to decide whether they will receive salbutamol in combination with placebo first (study day A) or salbutamol in combination with propranolol (study day B). All measurements during the two study days are identical. Both study days will be performed in the morning after an overnight fast. This means that subjects are not allowed to drink (except water) and eat from 10 PM the evening before, until arrival in the morning. Furthermore, subjects will be asked:

- not to exercise 48 hours in advance;
- not to drink alcohol 24 hours in advance;
- not to drink tea or coffee 24 hours in advance;
- to eat a standardized meal the evening before (options will be given by the researcher).

An overview of the timeline of the two study days and the involved study procedures is given in figure 4.

[figure not shown]

Figure 4 Study procedures.

After arrival anthropometric measurements (including heart rate and blood pressure) will be determined. An intravenous catheter will be placed and a baseline blood sample will be drawn. This will be followed by a resting energy expenditure (REE) measurement for 30 minutes using indirect calorimetry. Directly after the REE measurement subjects will receive either placebo (study day A) or propranolol (study day B). After 60 minutes, heart rate and blood pressure will be measured again (not shown in figure). Then subjects will be placed in the PET/CT scanner and salbutamol will be administered, directly followed by  $[^{18}\text{F}]\text{FDG}$  insertion. First, a low dose CT scan will be performed, followed by dynamic PET acquisition for 60 minutes. While scanning heart rate and rhythm will continuously be monitored. After PET/CT acquisition a blood sample will be drawn, heart rate and blood pressure will be measured and finally REE will be measured for another 30 minutes.

*Anthropometric measurements*

Shortly after arrival (8:00 AM), anthropometric measurements will be performed (weight, height, waist and hip circumference) and heart rate and blood pressure will be measured.

*Blood sampling*

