Next, in both arms a catheter will be inserted in an antecubital vein, for venous blood sampling and for administration of salbutamol and [ $^{18}\text{F}$ ]FDG tracer later during the study day. At two timepoints fasted blood samples will be collected: at the start of the study day and after PET/CT acquisition. In these samples we will determine markers for lipid metabolism (TC, FFA, TG, HDL-C, LDL-C, lipidomics) and glucose metabolism (glucose, insulin). Blood for these measurements will be collected in SST®II Advance Gel tubes of 8 mL and blood collection tubes containing ethylenediaminetetraacetic acid (EDTA) of 8 mL. In addition, we will measure electrolytes (sodium, potassium) in a heparin-lithium tube of 4 mL.

The heparin-lithium tube will directly be brought to the Department of Clinical Chemistry in the LUMC to quickly obtain information about electrolyte levels. The EDTA tube will after blood collection immediately be put on ice and centrifuged promptly (2,000 g at 4°C, for 10 minutes). The SST®II Advance Gel tubes must coagulate for 30-45 minutes before centrifugation. After centrifugation plasma and serum from both tubes will be divided in separate plastic tubes and frozen (-80°C) until assay. Material of all included patients from the SST®II Advance Gel tubes and EDTA tubes will be collected first and then above research markers will be determined all at once at the Department of Endocrinology of the LUMC. The 'rest material' will be stored in the LUMC Biobank Endocriene Ziekten for later additional analysis. For this material the rules and regulations of the LUMC Biobank Endocriene Ziekten are applicable.

An overview of the blood collection during the screening and the study days is provided in table 3.

Table 3 Blood collection during screening visit and study days

| Timepoint         | Measurement                                                                                                                      | Tubes                                                                                   | Amount                                           |
|-------------------|----------------------------------------------------------------------------------------------------------------------------------|-----------------------------------------------------------------------------------------|--------------------------------------------------|

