### 9.1 Primary study parameter

Our primary study parameter is glucose uptake by BAT, as measured by dynamic [ $^{18}\text{F}$ ]FDG PET acquisition. Patlak graphical analysis method [43] will be used to determine the fractional extraction of [ $^{18}\text{F}$ ]FDG ( $K_i$ ) in BAT

([http://www.turkupetcentre.net/petanalysis/model\\_patlak\\_interpretation.html](http://www.turkupetcentre.net/petanalysis/model_patlak_interpretation.html)). Patlak analysis will be based on the plasma input curve (time-radioactivity curve from the aorta), the BAT time-radioactivity curve, and the time in which [ $^{18}\text{F}$ ]FDG has reached steady-state in BAT (approximately 8-10 minutes). Based in the  $K_i$  we will calculate metabolic rate of glucose (MRglu).

$\text{MRglu} = (\text{Glucose concentration in plasma} / \text{Lumped constant}) * K_i$ .

(Lumped constant = 1.14 for adipose tissue)

- Differences between the effect of salbutamol in combination with placebo, and salbutamol in combination with propranolol will be assessed by paired-sample t-test or Mann-Whitney test.

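### The primary endpoint needs plasma glucose during the scan, but glucose is drawn only before any study drug and after the scan, and section 9.1 does not say which value is used

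*Protocol*

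**What the plan says.** Section 3.4 fixes the endpoint: "For this study the main outcome parameter is net glucose uptake by BAT after administration of salbutamol". Section 9.1 derives it in two steps. Patlak analysis gives Ki, using data from the time FDG reaches steady state in BAT, put at roughly 8-10 minutes. From Ki, "we will calculate metabolic rate of glucose (MRglu"). The multiplier is given only as "Glucose concentration in plasma", divided by a lumped constant of 1.14. No sample is named.

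Section 7.3.2 sets the blood draws: "At two timepoints fasted blood samples will be collected: at the start of the study day and after PET/CT acquisition". Glucose is among the analytes. The order of the day places the first draw before everything else: "An intravenous catheter will be placed and a baseline blood sample will be drawn", then a 30-minute REE measurement, and then "Directly after the REE measurement subjects will receive either placebo (study day A) or propranolol (study day B"). An hour of rest follows, then salbutamol over 5 minutes, FDG directly afterwards, and a 60-minute dynamic acquisition. The second draw comes after that acquisition. Table 3 agrees, with four 20 mL collections over two days.

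Section 7.1.2 lists "Serum markers for glucose metabolism (glucose, insulin") among the outcomes, and section 9.2 compares them between the two treatment days.

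**The concern.** MRglu is proportional to the glucose value entered. The value that belongs in the formula is the level during the period over which Ki is fitted, and no scheduled sample lies in that period. An error equal on both days would only rescale the contrast. An error that differs between days is a treatment-dependent error in the primary endpoint, and pairing does not remove it.

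The protocol gives a reason not to take glucose as constant. It studies the effect of salbutamol on glucose markers as a secondary objective, and it gives propranolol to block the action of salbutamol. If glucose does respond, the response could well differ by day. With ten subjects there is little room for a lost part of the effect.

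**Working it through.** **Timing (section 7.3.2).** From the first sample to FDG: 30 min REE + 60 min rest + 5 min injection = 95 min at least. The second sample falls at least 60 min after FDG. The fitting window is about 8-10 to 60 min after FDG. Blood volume check: 7.5 + 4 × 20 = 87.5 mL, so there are two samples per study day and no others.

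**The plan's own sample size (section 3.4).** Difference 13, SD 10, alpha 0.01 (taken as two-sided), power 80%.
- n = (t for alpha/2 + t for 80% power)² × (10/13)². With 10 degrees of freedom: (3.169 + 0.879)² × 0.592 = 9.70. With 9: (3.250 + 0.883)² × 0.592 = 10.11.
- The stated 10 is reproduced to within one subject. The exact noncentral t calculation gives 77.7% power at n = 10 and needs n = 11 for 80%. I use 77.7% as the reference.

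**Effect of a glucose error on the placebo day only.** If scan glucose exceeds the value used by a fraction x, the computed MRglu is the true value divided by (1 + x). Section 3.4 expects 22 on the placebo day and 9 on the propranolol day. The range for x is assumed, since the protocol gives none. Power is the paired t-test at n = 10 with SD held at 10: noncentrality = difference × √10 / 10, critical t 3.250.

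| x | Computed MRglu, placebo day | Shortfall | Share of 13 | Difference | Power |
|---|---|---|---|---|---|
| 0 | 22.0 | 0 | 0% | 13.0 | 77.7% |
| 5% | 22/1.05 = 20.95 | 1.0 | 8% | 11.95 | 69% |
| 10% | 22/1.10 = 20.0 | 2.0 | 15% | 11.0 | 60% |
| 20% | 22/1.20 = 18.33 | 3.7 | 28% | 9.33 | 44% |

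In the other direction, a value 5% or 20% above scan glucose gives 22 × 1.05 − 9 = 14.1 or 22 × 1.20 − 9 = 17.4.

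**Which sample is used matters.** Let glucose on the placebo day rise from FDG onward to an excess of 10% or 20% along four assumed courses. Let m be the mean excess over 10-60 min and g the excess in the value used. The error in MRglu is (1 + g)/(1 + m) − 1. Example, 20% plateau reached at 20 min: m = 0.19, so the start-of-day value gives 1/1.19 − 1 = −16.0% and the post-scan value 1.20/1.19 − 1 = +0.8%. The last column averages readings at 0, 30 and 60 min as (g0 + 2·g30 + g60)/4.

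| Assumed course (10% / 20%) | Start-of-day value | Post-scan value | Mean of 0 and 60 min | Time-average of 0, 30, 60 min |
|---|---|---|---|---|
| Steady rise to 60 min | −5.5 / −10.4% | +3.9 / +7.5% | −0.8 / −1.5% | −0.8 / −1.5% |
| Peak at 30, baseline at 60 | −5.4 / −10.2% | −5.4 / −10.2% | −5.4 / −10.2% | −0.6 / −1.2% |
| Plateau from 20 min | −8.7 / −16.0% | +0.5 / +0.8% | −4.1 / −7.6% | −1.8 / −3.4% |
| Peak at 30, half at 60 | −6.7 / −12.5% | −2.0 / −3.8% | −4.3 / −8.2% | −0.8 / −1.6% |

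The start-of-day value misses the change under every course. The post-scan value is near exact for a plateau and wrong in either direction otherwise. A mid-scan reading keeps the error within about 3.4% in all four.

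**False positives.** With equal Ki on both days and a 10% error on one day, the false difference is 0.9 (at level 9) to 2.2 (at level 22), and the rejection rate is 1.2% to 2.4% instead of 1%. At 20% it is 1.9% to 7.8%.

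**The case against.** The strongest reply is that the documents never say glucose will change. Section 12.1(i) names the expected effects as BAT glucose uptake, free fatty acids, glycerol and REE, not plasma glucose, and raised glucose is not among the side effects of concern in section 5.4. Confining the change to the placebo day further assumes that propranolol abolishes it. All of this stands, so the point is conditional and its size is an assumption.

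A second reply is that naming the sample is ordinary SAP content, and that the post-scan value, taken after both drugs on both days and close to the end of the fitting window, may be quite adequate. This stands in part. A reader might infer that section 9.1 permits the pre-drug value; it is merely silent, and a SAP may already exclude it. But a SAP can only choose between the two samples; it cannot supply a reading that was never drawn. Section 5.5 reports that tachycardia after a salbutamol bolus lasted around 30 minutes. That is heart rate and not glucose, but it shows that a response to a bolus can come and go within the scan, in which case a post-scan sample would miss it.

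A third reply is that Ki, which contains no glucose term, is already calculated in section 9.1 and named as an aim in section 1.6. That is correct and limits the harm. Net glucose uptake nevertheless remains the stated main outcome.

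**Conclusion.** The point holds as a gap in the sampling schedule with a conditional consequence. No glucose sample falls in the period that the primary endpoint describes, and the glucose term is left open. If glucose on the placebo day alone is 5-20% above the value used, MRglu there is understated by 1.0-3.7 nmol/g/min, 8-28% of the target, and power falls from 77.7% to between 69% and 44%. This rests on an assumed range, on the section 3.4 values of 22 and 9, and on an unchanged SD of 10.

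Three stronger readings are not supported. The documents do not show that glucose differs between the days. The error need not be material: it is close to zero if glucose levels off and the post-scan value is used. Nor would it readily produce a false positive: in the scenario quantified, it lowers the arm expected to be higher and so shrinks the contrast. An error the other way would inflate the contrast, but would be unlikely to create a difference of 13 by itself. This is a cheap improvement to make before the first study day, not a fault that invalidates the design.

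**What to change.** - **Section 7.3.2 and Table 3:** add a small glucose draw through the sampling catheter already in place, just before FDG, and one at mid-scan if it can be taken without disturbing the acquisition. The nuclear medicine team should confirm this. The mid-scan draw brings most of the gain. In the illustrations, averaging only a pre-FDG and a post-scan value is not uniformly better than the post-scan value alone.
- **Section 9.1:** exclude the start-of-day value from MRglu. Define the glucose term as the time-average of the scan-period and post-scan values, calculated in the same way on both days. Report Ki alongside as the glucose-free analysis.
- **If no draw can be added:** state that the post-scan value is used on both days, again with Ki alongside.

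The cost is about 2-4 mL more blood per study day and an update of the 87.5 mL total (4-8 mL over two days, so 91.5-95.5 mL). The fallback needs only a sentence in section 9.1.

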#### *Dynamic [ $^{18}\text{F}$ ]FDG PET/CT*

A dynamic [ $^{18}\text{F}$ ]FDG PET/CT scan will be performed to determine glucose uptake by supraclavicular BAT. Scans will be performed on a digital PET-CT scanner (Vereos; Philips Healthcare, Best, The Netherlands) available at the department of Radiology, section of nuclear medicine, of the LUMC in collaboration with Nuclear medicine physician Dr. [name] and medical physicist dr. [name]. The scanning protocol is based on the protocol regularly used by our collaborator Dr. [name][17]. First a low dose (30 mA, effective dose 0.7 mSv) CT scan of cervicothoracic area centered on the supraclavicular region will be performed, to locate PET regions of interest and used for attenuation correction of the PET-image. This will immediately be followed by a 60 min dynamic list-mode PET acquisition. For two scans this will lead to a total radiation burden of 8.4 mSv, which is below the threshold of 10 mSv [appendix A]. The list-mode data will be reconstructed into the following 35 temporal frames: 12 frames x 10 sec, 8 frames x 30 sec, 6 frames x 90 sec and 9 frames x 300 sec.

#### *Heart rate and blood pressure measurements*

During the study day we will monitor heart rate and blood pressure using a cuff connected to a digital blood pressure device at three set time points (at the start of the study day, before administration of salbutamol and after PET/CT scan). In addition we will monitor heart rate and -rhythm during PET/CT scan using a 3-lead ECG connected to a bedside patient monitor (Philips Intellivue MP5).

### **7.4 Withdrawal of individual subjects**

Subjects can leave the study at any time for any reason if they wish to do so without any consequences. The investigator can decide to withdraw a subject from the study for urgent medical reasons.

### **7.5 Replacement of individual subjects after withdrawal**

When a subject leaves the study, the investigator will try finding a replacement in order to maintain the initial population size. The newly recruited subject must comply with the established inclusion- and exclusion criteria.

**7.6 Follow-up of subjects withdrawn from treatment**

After a subject's withdrawal, he will be followed at the KRIG by the responsible investigator as frequently as necessary. If necessary, another specialist will be consulted, or the patient will be referred to a specialist for further treatment or investigation.

**7.7 Premature termination of the study**

We assume it would be unlikely that the study will be terminated prematurely due to the study method. Subjects will undergo a screening to minimize most severe side-effects known from IV salbutamol and propranolol. During the study days vital signs and potassium will be controlled at several set time points. This method is performed previously in the Centre for Human Drug Research (CHDR) without any severe side effects or complications [28]. In the unlikely case we do have to terminate our study prematurely we will perform data analysis on the subjects we have included.

## 8. SAFETY REPORTING

### 8.1 Temporary halt for reasons of subject safety

In accordance to section 10, subsection 4, of the WMO, the sponsor will suspend the study if there is sufficient ground that continuation of the study will jeopardize subject health or safety. The sponsor will notify the accredited METC without undue delay of a temporary halt including the reason for such an action. The study will be suspended pending a further positive decision by the accredited METC. The investigator will take care that all subjects are kept informed.

### 8.2 AEs, SAEs and SUSARs

#### 8.2.1 Adverse events (AEs)

Adverse events are defined as any undesirable experience occurring to a subject during the study, whether or not considered related to the investigational product, trial procedure or the experimental intervention. All adverse events reported spontaneously by the subject or observed by the investigator or his staff will be recorded.

#### 8.2.2 Serious adverse events (SAEs)

A serious adverse event is any untoward medical occurrence or effect that:

- results in death;
- is life threatening (at the time of the event);
- requires hospitalization or prolongation of existing inpatients' hospitalization;
- results in persistent or significant disability or incapacity;
- is a congenital anomaly or birth defect; or
- any other important medical event that did not result in any of the outcomes listed above due to medical or surgical intervention but could have been based upon appropriate judgement by the investigator.

An elective hospital admission will not be considered as a serious adverse event.

The investigator will report all SAEs to the sponsor without undue delay after obtaining knowledge of the events. The sponsor will report the SAEs through the web portal *ToetsingOnline* to the accredited METC that approved the protocol, within 7 days of first knowledge for SAEs that result in death or are life threatening followed by a period of maximum of 8 days to complete the initial preliminary report.

All other SAEs will be reported within a period of maximum 15 days after the sponsor has first knowledge of the serious adverse events.

### 8.2.3 Suspected unexpected serious adverse reactions (SUSARs)

Adverse reactions are all untoward and unintended responses to an investigational product related to any dose administered.

Unexpected adverse reactions are SUSARs if the following three conditions are met:

- the event must be serious (see chapter 9.2.2);
- there must be a certain degree of probability that the event is a harmful and an undesirable reaction to the medicinal product under investigation, regardless of the administered dose;
- the adverse reaction must be unexpected, that is to say, the nature and severity of the adverse reaction are not in agreement with the product information as recorded in: Summary of Product Characteristics (SPC) for an authorized medicinal product; Investigator's Brochure for an unauthorized medicinal product.

The sponsor will report expedited the following SUSARs through the web portal *ToetsingOnline* to the METC:

- SUSARs that have arisen in the clinical trial that was assessed by the METC;
- SUSARs that have arisen in other clinical trials of the same sponsor and with the same medicinal product, and that could have consequences for the safety of the subjects involved in the clinical trial that was assessed by the METC.

The remaining SUSARs are recorded in an overview list (line-listing) that will be submitted once every half year to the METC. This line-listing provides an overview of all SUSARs from the study medicine, accompanied by a brief report highlighting the main points of concern.

The expedited reporting of SUSARs through the web portal Eudravigilance or *ToetsingOnline* is sufficient as notification to the competent authority.

The sponsor will report expedited all SUSARs to the competent authorities in other Member States, according to the requirements of the Member States.

The expedited reporting will occur not later than 15 days after the sponsor has first knowledge of the adverse reactions. For fatal or life-threatening cases, the term will be maximal 7 days for a preliminary report with another 8 days for completion of the report.

### 8.3 Annual safety report

In addition to the expedited reporting of SUSARs, the sponsor will submit, once a year throughout the clinical trial, a safety report to the accredited METC, competent authority, and competent authorities of the concerned Member States.

This safety report consists of:

- a list of all suspected (unexpected or expected) serious adverse reactions, along with an aggregated summary table of all reported serious adverse reactions, ordered by organ system, per study;
- a report concerning the safety of the subjects, consisting of a complete safety analysis and an evaluation of the balance between the efficacy and the harmfulness of the medicine under investigation.

